## Abstract

**Background:**

Emotion regulation has been identified as an important transdiagnostic factor relevant to the treatment of mental health disorders. Many empirically validated psychotherapeutic treatments incorporate elements targeting emotion regulation. Most of these treatment approaches are conceptualized as standard face-to-face treatments not as blended treatments, which include an internet-based intervention.

**Objective:**

The aim of this study is to examine, for the first time, a new internet-based intervention—REMOTION—that will be provided transdiagnostically, as an add-on to psychotherapy, to provide a blended treatment format.

**Methods:**

A total of 70 participants will be assigned (1:1 allocation ratio) to either the intervention group (REMOTION + psychotherapy) or the treatment-as-usual group that receives psychotherapy alone. To maximize external validity, a typical outpatient treatment sample of patients diagnosed with a range of disorders such as depression, anxiety disorders, and adjustment disorder will be recruited from a university outpatient clinic. Patients with bipolar disorder, psychotic disorders, or acute suicidality will be excluded from the study. The feasibility and potential effectiveness of the intervention will be examined by assessing data at baseline, 6 weeks (post), and 12 weeks (follow-up). The primary outcome is general symptom severity, assessed with the Brief Symptom Inventory. Secondary outcomes are emotion regulation, depressive symptoms, anxiety symptoms, health related quality of life, well-being, and a variety of feasibility parameters. Quantitative data will be analyzed on an intention-to-treat basis.

**Results:**

Participant recruitment and data collection started in February 2020, and as of November 2020, are ongoing. Results for the study are expected in 2022.

**Conclusions:**

This pilot randomized controlled trial will inform future studies using transdiagnostic blended treatment.

**Trial Registration:**

ClinicalTrials.gov NCT04262726; http://clinicaltrials.gov/ct2/show/NCT04262726

**International Registered Report Identifier (IRRID):**

DERR1-10.2196/20936

## Introduction

### Emotion Regulation and Mental Health

According to Gross [1], emotion regulation refers to “the processes by which individuals influence which emotions they have, when they have them, and how they experience and express these emotions.” Emotion regulation can describe how individuals modulate the intensity or duration of an emotion and or the quality of an emotional response; it is often a conscious process, however, can also be an unconscious one [2].

According to several theoretical frameworks, successful emotion regulation is associated with positive health outcomes [3]. In recent years, research has continually shown that emotion regulation is an important transdiagnostic factor relevant to the treatment of mental health disorders [3-5]. Emotion regulation deficits play a role in the development, maintenance, and treatment of a variety of mental health disorders [6]. A number of empirically validated psychotherapeutic treatments incorporate elements of emotion regulation. For example, elements concerning emotion regulation can be found in the Unified Protocol for Transdiagnostic Treatment of Emotional Disorders [7], dialectical behavior therapy [8], accelerated experiential-dynamic psychotherapy [9], and emotion-focused therapy [10].

### Treatments Specifically for Emotion Regulation

Over the past years, there has also been an increase in treatment programs which explicitly target emotion regulation in order to improve mental illness symptoms. Many of these treatments have been carefully developed, and effectiveness has been shown in a number of trials. Examples are acceptance-based emotion regulation group therapy [11]; affect regulation training [12]; emotion regulation therapy [13]; Managing Emotions: Emotions Under Control [14]; Group Therapy for the Improvement of Emotion Regulation Skills [15]; and Gross model–based emotion regulation strategies training on anger reduction [16].

Notably, some of these treatment concepts have also made links to findings from research in basic affective science. Berking and colleagues [17], for example, have integrated findings from affective neuroscience in affect regulation training; they present 7 neural “vicious cycles” important to emotion regulation which are then complemented with 7 skills that are trained in sequence for adaptive emotion regulation. The effects of affect regulation training have been shown in several studies [17,18]. Gratz and Gunderson [11] developed emotion regulation group therapy by using a definition that draws on theoretical literature on emotion regulation during childhood and development, and places emphasis on the control of behavior while experiencing an emotion instead of control of the emotion [11]. Emotion regulation group therapy has shown effectiveness in several studies, and mechanisms of change have also been studied [11,19,20]. Emotion regulation therapy [21,22] also includes links to affective science by targeting motivational awareness, the development of regulatory capacities, and contextual learning [23] while making reference to theory by Gross [1]. In line with Gross’ differentiation of antecedent and response-focused strategies, emotion regulation therapy first teaches individuals adaptive response-focused strategies and then antecedent-focused strategies [24].

### The Extended Process Model of Emotion Regulation

In 2015, Gross presented a valuable extension to the process model of emotion regulation, named the extended process model of emotion regulation [2], elaborating that emotion regulation is an interaction of valuation systems and identifying emotion regulation stages: identification, selection, and implementation. The identification stage is concerned with whether to regulate emotion, the selection stage is concerned with what strategy should be used to regulate emotion, and the implementation stage is concerned with implementing a specific tactic suited to the situation [2]. Furthermore, Gross [2] also mentions the importance of flexibility in emotion regulation, described as matching strategy to circumstance.

A valuable contribution by Gross et al [25] described how elements from the extended process model of emotion regulation pertain to mental illness; maladaptive affect regulation can arise from identification, selection, implementation, and monitoring decisions and individuals can benefit from different treatment aspects and exercises depending on which stage of the model is affected. The intervention in this study, REMOTION, aims to use the stages of emotion regulation of the extended process model of emotion regulation [2] as a general framework for a highly structured transdiagnostic intervention. This intervention aims to foster the use of emotion regulation strategies, while also addressing potential difficulties encountered at each stage of regulation and focuses on training flexibility in emotion regulation strategy use.

### Over- and Underregulated Emotional States

In the field of psychotherapy research, the distinction between over- and underregulated emotional states and its relevance to psychotherapy have been made explicit [8,10,15,26]. According to Corcoran and colleagues [27], “one way to classify psychiatric disorders is to consider the degree to which emotions, reported within their syndromal presentation, are over or underregulated.” Greenberg [28] states that one guiding factor for integrative psychotherapy interventions may be the type of affect dysregulation involved (too little or too much emotion). Moreover, “whether clients are under- or overregulated and which emotions are to be regulated and how are important issues in any treatment [29]” . In accordance with this view, the same patient can experience both over- and underregulated states, and also exhibit patterns linked more closely to one or the other. Linehan [8,30] developed, in detail, distress tolerance skills relevant to overwhelming underregulated states.

On the other hand, more recently, radically open dialectical behavior therapy was developed for individuals with disorders characterized by overcontrol [26,31,32]. Emotional loneliness is seen as an important problem in disorders characterized by overcontrol [31]. The treatment is aimed at increasing flexible responding, prosocial signaling, openness, and emotional expressiveness of patients while reducing rigid inhibitory control [32]. Within radically open dialectical behavior therapy, specific skills for individuals with overcontrol problems have been developed [26]. REMOTION provides explicit strategies for both over- and underregulated states as described by Linehan [8] and Lynch [26], in a blended therapy format.

### Internet-Based Interventions

Over the last decades, the use of internet-based interventions has increased rapidly in the health sector and also in psychotherapeutic treatment. Internet-based interventions have become a popular and effective treatment format for the treatment of a variety of mental health disorders in various countries [33-39]; this has been shown mainly for internet-based cognitive behavioral therapy interventions but also for other treatment contents [40]. Such treatments often allow for more flexibility and convenience in use for the patient [41]. With regard to internet interventions focusing on emotion regulation, González-Robles and colleagues [42] have very recently published a study investigating the effect of an emotion-focused, guided internet treatment in specialized care; the internet intervention was superior to treatment as usual on measures of depression, anxiety, and health-related quality of life.

### Blended Treatment

The combination of internet interventions with conventional face-to-face therapy (blended treatment) is only in its early stages, and studies in a routine care setting are rare. Available studies on blended treatment in routine patient care show positive effects or positive trends for blended treatment [43-47]. For example, a study by Berger and colleagues [34] was able to show that a combination of psychotherapy and internet-based treatment was more effective than psychotherapy alone. Furthermore, Rizvi and colleagues [48], piloted an adjunct treatment for dialectical behavioral therapy called DBT Coach. DBT Coach was given to patients with borderline personality disorder and substance use for 10 to 14 days during outpatient treatment. A decrease of depressive symptoms and general distress was reported [48]. Moreover, Lukas and colleagues [49] piloted a blended therapy emotion regulation approach for individuals with elevated levels of alexithymia that showed positive effects on reducing alexithymia scores.

According to Erbe and colleagues [46], in comparison to purely internet-based treatments or purely face-to-face therapy, blended treatments could offer the following benefits: cost-effectiveness, increased effectiveness of treatment, improved transfer to everyday life, and ability to reach individuals for whom sole face-to-face or internet-based approaches are not suitable. A further benefit of providing interventions in a blended therapy format instead of solely internet-based is the argument that patient emotion regulation is assisted by the therapeutic relationship in session [10,50].

### Study Objectives

This study aims to pilot a blended treatment that uses an internet-based transdiagnostic program to improve emotion regulation (REMOTION) as an add-on to outpatient face-to-face psychotherapy. REMOTION aims to incorporate a variety of elements from effective treatment approaches into the emotion regulation framework provided by Gross [2], while also making explicit to patients specific strategies for over- and underregulated states [8,10,26]. The study aims to make use of the benefits of blended therapy format in order to convey emotion regulation skills to patients who are in psychotherapy. REMOTION aims to be a resource for both patient and therapist. This study aims to evaluate the feasibility and first effects of a transdiagnostic, blended treatment focused on emotion regulation in a mixed outpatient sample.

## Methods

### Study Design

The study is a 2-arm pilot randomized controlled trial comparing an intervention group (REMOTION + psychotherapy) with a treatment as usual group (psychotherapy alone). Participants in the intervention group will immediately be given access to REMOTION whereas participants in the treatment as usual group will receive access to REMOTION after 12 weeks. Assessments will occur at baseline, 6 weeks (post), and 12 weeks (follow-up) for all participants. Assessment at 6 and 12 weeks will occur irrespective of whether the patient is still in face-to-face treatment. Figure 1 depicts the design of the trial. The single center trial will take place at the outpatient clinic of the Department of Clinical Psychology and Psychotherapy at the University of Bern, Switzerland.

**Figure 1 figure1:**
[figure not shown]
Participant flow. TAU: treatment as usual.

### Sample Size

According to Sim and Lewis [51], 55 participants are the minimum necessary for a pilot trial. Moreover, according to Whitehead and colleagues [52], for a main trial designed with 90% power and 2-sided 5% significance, 25 participants per treatment arm are necessary in the pilot for standardized effect sizes that are small. Furthermore, previous unpublished data at the outpatient clinic for psychotherapy at the University of Bern has shown dropout rates of 15%. Therefore, a final sample size of 70 is planned for the study (35 per trial arm).

### Eligibility Criteria

The inclusion criteria are age over 18 years, in psychotherapeutic treatment, with mental illness, with internet access, and who provide written informed consent. The exclusion criteria are current participation in another intervention specifically for emotion regulation, a current episode or a history of psychotic disorders or bipolar disorder, acute suicidality, and not fluent in the German language.

### Recruitment, Randomization, and Blinding

Patients registering at the outpatient clinic will be informed about the study. Interested patients receive an information sheet, are invited to ask questions, and can provide written informed consent if they wish to participate. After study eligibility is proven, participants are randomly assigned to 1 of 2 groups (intervention or treatment as usual). Participants are randomized using a computerized random number generator and randomly permuted block sizes. The allocation schedule is generated by a researcher not involved in the research process and is unknown to the investigators and participants. There is no blinding implemented in the study, consistent with recommendations for the conduct of pragmatic randomized controlled trials in routine practice [53], in which the focus is on external validity and generalizability of the results to routine practice.

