### Intervention

#### REMOTION

REMOTION is an internet-based program that was created at the University of Bern (by [name] in collaboration TB and with input from FM). A more detailed description of the program can be found in Table 1. It is a 6-part program (introduction and 5 modules), and the general sequence and components of the modules are based on the stages of emotion regulation in the extended process model [2]. A variety of elements from different evidence-based psychotherapeutic treatment approaches—dialectical behavior therapy [8], emotion-focused therapy [10], cognitive behavioral therapy [54], mindfulness based cognitive therapy [55], radically open dialectical behavior therapy [26], and Unified Protocol [7]—are incorporated into each module of REMOTION. Furthermore, the focus placed on overregulated as well as underregulated states as described by Greenberg [10] and Lynch [26].

**Table 1 table1:** REMOTION content.

Module	Content
Introduction	Information about the structure of the intervention, about the theoretical background, and a user guide are provided in this module.
Psychoeducation	Information is provided about what emotions are, what their functions are, and what types of emotional experiences there are. The concept of emotion regulation is introduced, and the relationship between emotion regulation and mental illness is explored.
Identification	Emotional awareness, which is identified as key to the perception substep of the identification stage of emotion regulation [2], is explored in this module. If and when to regulate emotions, along with information on the value of emotion regulation, are introduced in this module.
Selection	This module shows patients what types of emotion regulation strategies are available. The focus is on the selection of an emotion regulation strategy [2]. The strategies—situation selection or modification, attentional deployment, change of cognitions, and response modulation [1]—are introduced in this module. Furthermore, strategies specific to over- and underregulated states [10,26,30] are also introduced.
Implementation	This module shows patients how the previously introduced strategies can be implemented, for example, translated to different tactics [2]. Exercises are introduced for every emotion regulation strategy, and advice is provided as to how these exercises can be implemented into daily life.

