#### Primary Outcome Measure

The primary outcome measure in this study is general symptom severity as measured with the Brief Symptom Inventory (German version) [61]. The Brief Symptom Inventory will be given to patients at baseline, post and follow-up. The Brief Symptom Inventory contains 53 items and is one of the most frequently used questionnaires to measure general symptom severity. A study [62] has shown that it has good psychometric properties, comparable with those of the Symptom Checklist-90-Revised instrument .

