### Planned Analysis

Data will be analyzed on an intention-to-treat basis, meaning that all randomized patients will be included in the outcome analyses and missing data be handled accordingly. The primary outcome measure, general symptom severity, will initially be analyzed descriptively. Within- and between-group effect sizes will be calculated, and linear mixed models will be calculated. These models use all available data on a participant and estimate parameters of missing values. The various secondary outcomes will also be analyzed descriptively, then analyzed with linear mixed models, where applicable. With regard to feasibility parameters, the data will be characterized by descriptive statistics (means, standard deviations, and confidence intervals) in order to allow for comparison with other studies in the field. For categorical data, amount or percentage will be reported. The qualitative interviews generated for this study, will be analyzed using qualitative content analysis as recommended by Mayring [80]. Results will be reported in accordance with CONSORT (Consolidated Standards of Reporting Trials) [81] and CONSORT-EHEALTH [82].

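### Giving up all blinding on external-validity grounds does not justify leaving the data analysis unmasked, and coding the arms would be a cheap safeguard

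*Protocol article*

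**What the plan says.** Under Recruitment, Randomization, and Blinding, the article says: "There is no blinding implemented in the study, consistent with recommendations for the conduct of pragmatic randomized controlled trials in routine practice". It adds that these are trials "in which the focus is on external validity and generalizability of the results to routine practice". No role is exempted from the rule.

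The same section protects the allocation schedule: "The allocation schedule is generated by a researcher not involved in the research process and is unknown to the investigators and participants". That is concealment of upcoming assignments. It does not mask anyone once a patient has been assigned.

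On the origin of the program, the REMOTION section says: "REMOTION is an internet-based program that was created at the University of Bern". Study Design says: "The single center trial will take place at the outpatient clinic of the Department of Clinical Psychology and Psychotherapy at the University of Bern, Switzerland".

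On the analysis, Planned Analysis says: "Within- and between-group effect sizes will be calculated, and linear mixed models will be calculated". It fixes intention-to-treat and the use of all available data. It does not say who carries out the analysis.

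**The concern.** The rule covers more roles than its justification does. Patients know whether they have the program and therapists know whether they hold the booklet, so masking them is not practicable, and a pragmatic trial has good reason not to try. The analyst is in a different position. Hiding which coded arm is REMOTION has no effect on what patients receive, what therapists do or how far the results generalise.

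The gap matters somewhat more here because the program and the trial come from the same university. Data cleaning, handling of convergence problems and departures from plan all call for judgement. If these judgements are made with the arms visible, they can lean, even unintentionally, towards REMOTION. The primary outcome, the Brief Symptom Inventory, is already self-reported by unmasked patients. A leaning analysis could add to that bias in the same direction, and this second source can be reduced cheaply.

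**Working it through.** **Does the stated reason cover the stated rule?**

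| Role | Knows the arm by design? | Does external validity argue against masking? |
|---|---|---|
| Patient | Yes: program access at once or after 12 weeks (Study Design) | Yes |
| Therapist | Yes: information booklet and integration into sessions (REMOTION) | Yes |
| Staff giving access, sending reminders, interviewing | Yes | Yes, they need the allocation for their work |
| Person cleaning data and fitting between-arm models | Not necessarily | No, routine care is unaffected |

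The reason fails only in the last row, and the rule makes no exception for it.

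**How much could directional choice matter?** The article gives no figure to reproduce, so this is an illustration.

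Inputs:
- Patients per arm: 35 × (1 − 0.15) = 29.75, taken as 30. The 35 and the 15% dropout are in Sample Size.
- Number of defensible analyses: 4 (assumed).
- Correlation ρ between their test statistics: 0.8 or 0.9 (assumed).
- Selection rule: the analysis most favourable to REMOTION is kept, with no true difference (assumed).

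Shift in the expected effect, in SD units:
- Standard error of a standardised mean difference: √(2/30) = 0.258.
- The expected maximum of 4 independent standard normals is 1.029. With equal correlation ρ, the expected maximum z is √(1 − ρ) × 1.029.
- ρ = 0.8: √0.2 × 1.029 = 0.460, and 0.460 × 0.258 = 0.119 SD.
- ρ = 0.9: √0.1 × 1.029 = 0.326, and 0.326 × 0.258 = 0.084 SD.

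False positives favouring REMOTION, P(max z > 1.96), by numerical integration:
- One analysis fixed in advance: 2.5%.
- ρ = 0.8: 5.7%.
- ρ = 0.9: 4.7%.

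**What would A/B coding change?** Without knowing which arm is REMOTION, an analyst cannot choose in its favour, so the directional shift goes. The analyst could still pick the smallest p-value among the 4. The chance that at least one has |z| > 1.96 in either direction is about 11% (ρ = 0.8) or 9% (ρ = 0.9), and it is the same with or without labels.

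**The case against.** The strongest reply is that the harm is inferred. A reader might conclude that the developers of REMOTION will choose the models while looking at the arms. The documents do not support that. No section names the analyst, and the shared institution shows an interest, not an analysis role. The model may also be fixed in an analysis plan that is not shown, and the article's brevity about the mixed model is no fault in itself. This stands, so the point is limited to what the rule permits. It does not remove the point: the no-blinding statement is categorical and its reason does not reach the analyst. A pre-specified model also leaves cleaning and departures from plan open to judgement.

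A second reply concerns size. A reader might set the 11% or 9% above against 5% as the error that masking would prevent. That is wrong on two counts: those figures count results favouring either arm, and coding the arms does not change them. If the most favourable analysis is kept, it reaches two-sided 5% in about 6.2% (ρ = 0.8) or 5.6% (ρ = 0.9) of cases. The distortion lies mainly in direction. Planned Analysis also states no significance threshold.

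A third reply is that masking is not free. Staff must know the allocation to give access, send reminders, hold interviews and monitor contamination, and several measures exist only in the REMOTION arm. This stands as a reason for new IDs and a split export. It is not a reason against masking the analysis file.

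Finally, this is a pilot that, under Limitations, promises only preliminary results on effects. This also stands, and keeps the consequence modest.

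**Conclusion.** The point holds in limited form. External validity justifies leaving patients and therapists unmasked; it does not justify extending the rule to data cleaning and the between-arm models. With the program created at the institution that runs the trial, the rule leaves room for directional analysis decisions. Whether anyone would use that room cannot be read from the article.

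Under the assumed 4 analyses, correlation 0.8 to 0.9 and 30 per arm, the most that such steering does is shift the expected null effect by about 0.08 to 0.12 SD and raise false positives favouring REMOTION from 2.5% to about 4.7-5.7%. The number of analyses, the correlation and the selection rule are not in the documents, so these figures show an order of magnitude and are not an estimate for this trial.

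Masking the analysis removes the directional part. It does not remove undirected selection among models, nor the bias from unblinded patients rating their own symptoms. It is a worthwhile, inexpensive improvement with a modest benefit in a pilot.

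**What to change.** Replace the blanket statement in Recruitment, Randomization, and Blinding with wording to this effect: *Patients and therapists are not blinded. Between-arm analyses of the Brief Symptom Inventory and of the other outcomes collected in both arms are run on an export with new IDs, arms coded A/B and REMOTION-only variables held back. The code is broken only after data cleaning and the primary model are final. REMOTION-only feasibility data are analysed from a separate file.*

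New IDs are needed because trial staff hold patient-level allocation, so relabelling the arms alone would hide little. The variables to hold back are adherence, usability, user experience, satisfaction and negative effects, all collected only in the REMOTION group.

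The cost is one extra recoded export and somewhat later unmasking. Sample size, assessment schedule and treatment in either arm are unchanged.
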